## Methods

### Study Design and Objectives

CIRT is a prospective, multicenter, single-device, noninterventional study of patients with liver tumors treated with radioembolization in daily routine practice as a standard of care. The primary objective is to observe the real-life clinical application of radioembolization and the impact of the treatment in clinical practice. This objective is described by: type of liver cancer, intention of treatment, prior hepatic procedures, associated systemic therapy, and postradioembolization hepatic procedures.

Secondary objectives are effectiveness, safety, technical considerations, and patient-reported outcome measures (see Textbox 1).

Secondary end points.

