**Figure 1 figure1:**
[figure not shown]
Flowchart of patient inclusion and measurement time points. CIRT: Cardiovascular and Interventional Radiological Society of Europe Registry for SIR-Spheres Therapy.

**Table 1 table1:** Time of measurement for each end point and associated measurements.

End point	Baseline measurement	Day of treatment measurement	Follow-up measurement
Real-life application of radioembolization	Type of liver cancer Prior hepatic procedures Associated systemic therapy (prior systemic therapy)	Intention of treatment	Postradioembolization hepatic procedures Postradioembolization systemic chemotherapy
Effectiveness end points	N/A^a^	Treatment date	Date of effectiveness event (OS^b^, PFS^c^, hepatic PFS, IR^d^)
Safety end points	N/A	Severe day of treatment complications (Grade 3-4)^e^	Adverse events (Grade 1-5)^e^ Abnormal laboratory values
Technical considerations end points	Patient-related characteristics Prior hepatic procedures Physical characteristics (body surface area, lung shunt study [%], Eastern Cooperative Oncology Group performance status)	Treatment planning Treatment administration Procedure-related outcomes	N/A
Patient-reported outcome end points	EORTC^f^ QLQ-C30^g^ Additional module for HCC^h^	N/A	EORTC QLQ-C30 Additional module for HCC

^a^N/A: not applicable.

^b^OS: overall survival.

^c^PFS: progression-free survival.

^d^IR: imaging response.

^e^Grading according to Common Terminology Criteria for Adverse Events version 4.03.

^f^EORTC: European Organisation for the Research and Treatment of Cancer.

^g^QLQ-C30: Quality of Life Questionnaire C30.

^h^HCC: hepatocellular carcinoma.

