### Statistical Analysis

All patients who were found eligible, enrolled in the registry, underwent radioembolization treatment, and have the minimum amount of data required will be included in analysis. Patients for which the amount of data collected is too scarce to warrant meaningful analysis will be excluded. The number of excluded patients and reason for exclusion will be reported.

Data regarding the primary end point, safety, and technical considerations will be presented by summaries (eg, counts, means, standard deviations) and descriptive statistics. The number of missing observations will be given in all summary tables. Time to event end points will be described graphically through the Kaplan-Meier analysis (including 95% CIs for median survival). The Cox regression will be used to assess the impact of the covariates for time to event end points (Table 2).

Hazard ratios and their 95% CIs will be presented together with *P* values. Sensitivity analyses of time to event data will be performed where censored patients with less than 6 weeks of follow-up will be included as worst case (ie, death or progression).

**Table 2 table2:** Covariates for time to event end points.

Covariate	Variables
Age (years)	≤69 and ≥70
Sex	Male, female
Number of lines of previous chemotherapy	0, 1, 2-5, ≥6
Primary tumor in situ	Yes, no
Eastern Cooperative Oncology Group performance status	0, 1, and ≥2
Presence of extrahepatic metastases	Yes, no
Prior liver procedures	Yes, no
Number of liver tumors	1, 2-5, and ≥6
Percentage tumor to liver volume	Continuous

QOL is measured with the EORTC QLQ-C30, a questionnaire developed to assess the QOL in patients with cancer. The QLQ-C30 includes five functional scales, three symptom scales, a global health status scale, and six single items. The functional and symptom status of the QLQ-C30 will be assessed according to the scoring manual developed and validated by EORTC [29]. Patients who die during follow-up will be included in the QOL analyses until their date of death. The focus of these analyses will be on patients who are alive at the time point of analysis.

To document the safety and effectiveness of radioembolization and subsequent surgical or interventional procedures, the data will be broken down into subgroups as defined for the covariate analyses above.

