### Conclusion

To date, the CIRT is the largest observational study on the use of radioembolization with 90Y resin microspheres. The objective of the study was to observe the real-life clinical application of radioembolization and its impact in clinical practice. Currently, radioembolization has a position in the guidelines for the treatment of HCC, cholangiocarcinoma, and mCRC, and more data is warranted on the possibilities that this treatment has for these diseases. Furthermore, additional data is needed for the effects of other lines of therapy and treatment of liver metastatic disease from other primary sites. Observing a large study population may reveal treatment aspects that would justify a wider application of this innovative treatment.

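### Type of liver cancer is missing from the fixed Cox covariate list and the subgroup rule tied to it, so covariate hazard ratios can reflect differences between diseases

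*Protocol article*

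**What the plan says.** - **Model.** Statistical Analysis: "The Cox regression will be used to assess the impact of the covariates for time to event end points (Table 2". Hazard ratios are to be reported with 95% confidence intervals and P values.
- **Covariates.** Table 2 lists nine: age, sex, lines of previous chemotherapy, primary tumor in situ, ECOG performance status, extrahepatic metastases, prior liver procedures, number of liver tumours, and percentage tumour to liver volume. The one closest to a diagnosis is "Primary tumor in situ", coded yes or no.
- **Subgroups.** For safety and effectiveness, "the data will be broken down into subgroups as defined for the covariate analyses above".
- **Role of tumour type elsewhere.** Study Design and Objectives puts it first among the descriptors of the primary objective: "This objective is described by: type of liver cancer, intention of treatment, prior hepatic procedures, associated systemic therapy, and postradioembolization hepatic procedures". Table 1 has it collected at baseline: "Type of liver cancer Prior hepatic procedures".
- **Population.** Site Selection and Patient Enrollment admits adults treated for any primary or secondary liver tumour. Results reports 1047 patients. Data Collection sets follow-up at no more than 24 months.

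**The concern.** The registry puts HCC, cholangiocarcinoma, colorectal metastases and metastases from other primaries into one cohort. Some Table 2 covariates are likely to be distributed differently across these diseases. Lines of previous chemotherapy is one. Primary tumor in situ is another, since its meaning changes when the liver tumour is itself the primary. If prognosis also differs by disease, a Cox model that ignores disease attributes part of that difference to the covariate. A reader would then take a published hazard ratio for prior chemotherapy as a prognostic effect when it partly describes who has which cancer.

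The subgroup rule repeats the gap. The Introduction and Discussion present data on less studied diseases as a reason for the registry, and the Conclusion says of HCC, cholangiocarcinoma and metastatic colorectal cancer that "more data is warranted on the possibilities that this treatment has for these diseases". The subgroups named would not show safety or effectiveness by disease.

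**Working it through.** **The text.** There is no sample size, event or power figure to reproduce; the article says that no formal calculation was made. Setting the sections side by side:

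1. Type of liver cancer is collected at baseline (Table 1) and leads the primary objective (Study Design and Objectives).
2. It is not among the nine covariates of Table 2.
3. The subgroup sentence refers back to those covariates, so it is not a named subgroup.
4. No section mentions stratification, separate models or separate Kaplan-Meier curves by disease.

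The omission is therefore in a list that the article states, with categories, and not only in detail left to another document.

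**The possible size.** From the article: N = 1047, follow-up capped at 24 months. Assumed, because the article gives no figures:

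- two tumour types, mixed 50:50, with exponential survival;
- median survival of 12 months in the reference type;
- hazard ratio h between types of 1.0 to 2.0;
- one binary covariate with prevalence p0 in the reference type and p1 in the other, and a true hazard ratio of 1.00 within each type.

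*Hand check.* With a 50:50 mix and p0 + p1 = 1, patients with the covariate are of the second type in proportion p1, and patients without it in proportion p0. At the start of follow-up the hazard ratio that ignores type is

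HR = (p1·h + p0) / (p0·h + p1).

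For h = 1.5 and prevalence 20% v 80%: (0.8 × 1.5 + 0.2) / (0.2 × 1.5 + 0.8) = 1.4 / 1.1 = 1.27.
For h = 2.0 and 10% v 90%: (0.9 × 2 + 0.1) / (0.1 × 2 + 0.9) = 1.9 / 1.1 = 1.73.
For h = 1.3 and 40% v 60%: (0.6 × 1.3 + 0.4) / (0.4 × 1.3 + 0.6) = 1.18 / 1.12 = 1.05.

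*Simulation.* 400 replicates per setting, Cox model without tumour type; rejection is at two-sided 5%:

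| Prevalence by type | h = 1.3 | h = 1.5 | h = 2.0 |
|---|---|---|---|
| 50% v 50% | HR 1.00, 5% | HR 1.00, 3% | HR 1.00, 7% |
| 40% v 60% | HR 1.06, 15% | HR 1.08, 23% | HR 1.14, 50% |
| 20% v 80% | HR 1.17, 58% | HR 1.27, 94% | HR 1.50, 100% |
| 10% v 90% | HR 1.23, 87% | HR 1.39, 100% | HR 1.72, 100% |

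With h = 1.0 the HR is 1.00 at every prevalence, with 3% to 5% rejection. The simulated hazard ratios agree with the hand formula to within about 0.01.

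With tumour type in the model, the HR is 0.99 to 1.01 and rejection about 4% to 7% in all 16 settings. The Monte Carlo standard error at a 5% rate is √(0.05 × 0.95 / 400) = 0.011, so these rates are compatible with 5%.

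**The case against.** Four replies deserve weight.

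*The article does not say that one model pools all diseases, or that these are the only subgroups.* This stands as a limit on wording. A reader might infer that effectiveness will never be broken down by disease, but the article supports only that no such breakdown is specified in it. A full protocol or SAP, not shown, could apply Table 2 within each disease. The point survives because the covariates and the subgroup rule are written out, and followed as written they leave tumour type out.

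*Confounding is conditional.* This also stands. Prognosis and covariate prevalence must both differ by type. If either does not, the table shows no bias. A reader might infer that the hazard ratios are confounded as a fact; the article has no figures that would establish it.

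*Other Table 2 covariates may absorb part of the difference.* This stands in part. The illustration uses one covariate, not the planned nine, so its values are not predictions for the full model. But yes/no items such as primary tumor in situ or extrahepatic metastases cannot tell HCC from cholangiocarcinoma, or colorectal from other metastases. Adjustment for them cannot be relied on to replace the diagnosis.

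*These are exploratory, secondary analyses.* This stands. The primary objective is descriptive, the article calls the registry descriptive and exploratory, and no treatment contrast rests on the Cox models. The Discussion voices a hope of insight into less explored populations, and the Conclusion describes a general need. Neither is a commitment to disease-specific estimates.

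**Conclusion.** The concern holds in a limited form. The article fixes a covariate list and a subgroup rule that both omit type of liver cancer, in a cohort open to any primary or secondary liver tumour, and it specifies no other analysis by disease. Hazard ratios for covariates whose distribution differs by tumour type can therefore reflect disease differences.

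The size is unknown from the article. Under the stated assumptions, the spurious HR for a covariate with no within-type effect runs from about 1.0 to about 1.7. The range depends on the assumed difference in prognosis (1.0 to 2.0) and in prevalence (none to 10% v 90%), and it leaves the other Table 2 covariates out of the model.

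A reader might also infer that HCC stage goes unused, because Data Collection records it and Table 2 lacks it. The article does not say so.

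This should be fixed before results are reported. It does not touch the descriptive primary objective.

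**What to change.** 1. Add type of liver cancer to Table 2, with at least HCC, cholangiocarcinoma, colorectal metastases and other metastases. Use it as a stratification factor, so that each type has its own baseline hazard, or state that the Cox models are fitted within type.
2. Name it as a subgroup for safety and effectiveness.
3. Give Kaplan-Meier estimates by type. A stratified model yields no hazard ratio for type, so these curves carry that information.
4. Interpret primary tumor in situ within secondary tumours, where it can vary independently of the diagnosis.

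Type is already recorded at baseline, so the cost is analysis wording and some extra tables and curves. The statistical cost is wider confidence intervals in the small tumour types, or sparse events there if models are fitted within type. Stratifying the common model limits the second problem.

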Missing data can be expected in the event of a study site failing to enter certain data into the e-CRF, or a patient’s withdrawal of consent or being lost to follow-up. Given the descriptive and exploratory nature of CIRT, all available data will be used, and no imputations of missing data will be made. The amount of missing data will be summarized and the subset of patients with missing data will be compared with patients included in the analysis.

In the effectiveness analyses, patients withdrawing consent or being lost to follow-up will be censored at the last time they were observed as being alive (overall survival) or at the time of their last magnetic resonance imaging scan from which disease progression could have been determined (progression-free survival [PFS]). Patients who die during the course of their follow-up in the registry will be regarded as having disease progression in the analyses of PFS and liver-specific PFS.

Missing data for QOL will be handled in line with the suggestions in the EORTC scoring manual for QLQ-C30; the amount of and reasons for completely missing forms will be analyzed and multiple imputations will be used for a part of the completely missing forms (ie, forms considered to be missing at random or due to administrative failure) [29].

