### Limitations

The single-arm observational study nature of the study design implies that several limitations need to be considered. The absence of a contemporaneous comparator group may limit our interpretation of the clinical data reported. Despite this, important positive features of the study are the long-term data collection for patients included and the valuable information collected on health-related QOL. The size of the study should enhance patient selection by providing new information on the patient subgroups that benefit most from this treatment in day-to-day clinical practice.

Furthermore, selection bias could occur at several stages of the study. An element of site selection was introduced when the Steering Committee created a list of sites that met the selection criteria of minimal expertise with radioembolization treatment. The potential of patient selection bias is addressed by a contractual agreed upon prospective design, whereby sites agreed to present the possibility to participate in the CIRT to all eligible patients consecutively.

Another source for bias relates to drop-out during follow-up. The sites included in the study have been advised to continue patient follow-up at least 24 months after the first treatment. However, patients may be lost to follow-up or withdraw their consent at any time. Loss to follow-up may relate to the course of disease or site procedures; for example, when a patient is treated at a participating site but followed-up by their referring physician, sometimes in another country. It will therefore not always be possible for study sites to collect additional follow-up data and the patient will be reported as lost to follow-up. Baseline characteristics will be compared between those lost to follow-up and those who have follow-up data to assess differences with the potential to bias results. Notable differences on a background characteristic will prompt additional analyses where the sensitivity of the results to that background characteristic will be further assessed.

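### Quality-of-life forms missing because the patient was too ill fall outside the planned imputation and have no stated sensitivity analysis, so change in quality of life among living patients can be reported too favourably

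*Protocol article*

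**What the plan says.** The Abstract lists change in quality of life among the secondary objectives. Under Data Collection, the questionnaire is given before treatment, shortly afterwards and at each follow-up, for at most 24 months.

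The Statistical Analysis section fixes three things for QOL:

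- **Population.** "Patients who die during follow-up will be included in the QOL analyses until their date of death", and then "The focus of these analyses will be on patients who are alive at the time point of analysis".
- **Imputation.** "multiple imputations will be used for a part of the completely missing forms", which the article spells out as "forms considered to be missing at random or due to administrative failure".
- **Description.** "the amount of and reasons for completely missing forms will be analyzed".

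The general missing-data rule in the same section is that "no imputations of missing data will be made". The only sensitivity analysis described there is a worst-case one for early-censored patients, and it covers time-to-event data only.

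The Limitations section concedes that there is no comparator and that loss to follow-up may depend on the course of disease. It also counts "the valuable information collected on health-related QOL" among the strengths of the study.

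**The concern.** Among living patients, wholly missing forms fall roughly into two kinds. Some are missing for reasons unrelated to the unseen score, or related to it only through data already recorded. The imputation rule covers these. Others are missing because the patient was too unwell to complete them. The rule leaves these out, and they are the ones whose absence pulls the average upward.

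The article recognises illness-related loss in its limitations and prepares a worst-case analysis for survival end points, but states nothing comparable for QOL. In a single-arm registry there is no control trajectory against which such drift would show. A reader of the results could take the average among returned forms as the experience of all living patients.

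**Working it through.** **No figure to reproduce.** The article gives no QOL mean, standard deviation, completion rate, survival rate or sample size calculation. The rule can only be tested for direction, with a range of sizes on assumed inputs.

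**From the article:** assessments about every 3 months to 24 months (8 visits), summary among the living, no stated imputation of illness-related forms.

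**Assumed (not in the article):** 200,000 simulated patients; baseline mean 65, SD 20 on a 0-100 scale; median survival about 12 months; about 25% of forms missing among the living; mean true slope 0, -1 or -2 points per quarter, with between-patient slope SD 3. The log-odds of a missing form rise by β per 10 points of worse QOL, and the log-odds of death rise by γ.

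**Measure.** Bias = mean change from own baseline in returned forms, minus the true mean change in all patients alive at that visit. The yardstick is the living, so any bias remains even if the while-alive summary is fully accepted.

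**Step 1: missingness and death unrelated to QOL (β = γ = 0), slope -1, 24 months.** -7.93 - (-7.99) = 0.06. No bias.

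**Step 2: only death depends on QOL (γ = 0.3, β = 0), slope -1, 24 months.** 1.40 - 1.51 = -0.11. No material bias for the while-alive summary, although it differs greatly from the underlying trend of -7.97. Survival selection alone changes what the number means. It does not make it wrong for the living.

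**Step 3: only form return depends on QOL (β = 0.3, γ = 0).**

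| Month | Slope | Forms returned by the living | Observed | True, living | Bias |
|---|---|---|---|---|---|
| 12 | 0 | 73% | +2.13 | +0.01 | 2.12 |
| 12 | -1 | 71% | -1.72 | -3.97 | 2.25 |
| 12 | -2 | 68% | -5.45 | -7.95 | 2.50 |
| 24 | 0 | 72% | +5.25 | +0.02 | 5.23 |
| 24 | -1 | 67% | -1.88 | -7.91 | 6.03 |
| 24 | -2 | 63% | -9.09 | -15.96 | 6.87 |

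**Step 4: death and return both depend on QOL (β = γ = 0.3), 24 months.** Slope -1: 5.49 - 1.71 = 3.78. Slope -2: -1.54 - (-5.57) = 4.03. With both at 0.5 and slope -2, the observed change is +2.85 against a true -1.79, so the sign can reverse.

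**Step 5: would imputation under missing at random cure it?** In step 3 at slope -1, 24 months, filling every missing form by regression on baseline gave -0.94 against -7.91, a gap of 6.97. This stand-in used baseline only. A model that also used each patient's earlier follow-up forms should recover part of the gap, but the part that depends on the current unseen score remains.

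**Step 6: how large a downward shift would be needed?** A shift of δ on imputed forms lowers the mean by f × δ, where f is the fraction of living patients with shifted forms. In that scenario at 24 months f = 0.33, so a shift of 15 moves the mean by 0.33 × 15 = 4.95, and closing the gap needs 6.97 / 0.33 = 21.1. At 12 months the gap is -0.88 - (-3.97) = 3.09 with f = 0.29, which needs 3.09 / 0.29 = 10.7.

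**The case against.** **The while-alive focus is not an error.** QOL after death is undefined, and summarising patients alive at each visit is standard. This stands, and step 2 bears it out. A reader might infer that the survivor focus itself invalidates the analysis. The article does not support that.

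**The effect is not certain.** A reader might infer that QOL will look preserved or improved. Step 1 shows no bias, and step 3 at slope -2 leaves a 9-point decline plainly visible. Larger apparent gains arise if the average of available forms is set against the whole cohort's baseline average, but the article does not prescribe that contrast. This stands too: the claim is that the result can be too favourable.

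**Safeguards are planned.** Reasons for missing forms will be analysed, patients with missing data compared with the rest, questionnaires sought by letter or phone, and those lost to follow-up compared at baseline, with further analyses if notable differences appear. These are real, and retrieval can reduce missingness. None corrects the estimate, and a comparison of baseline characteristics cannot detect deterioration after baseline.

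**Not imputing illness-related forms under missing at random is defensible.** The assumption would be doubtful there, and for forms that do meet it the planned imputation is useful. Both points are right. But declining to impute under a doubtful assumption leaves the forms out, which is no neutral choice.

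**Detail belongs in an analysis plan.** Model specification does, and the EORTC scoring manual to which the article defers is not at hand. The point here rests on the inclusion rule that the article itself states.

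**The two imputation statements.** A reader might see a contradiction. In context, the QOL paragraph reads as an exception to the general rule, so this is a matter of wording.

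**Conclusion.** The point holds in a limited form. Followed as written, the imputation rule leaves illness-related missing forms out of the QOL estimates among living patients, with no stated sensitivity analysis for them. The direction of bias is favourable whenever return depends on current health.

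The size cannot be derived from the article. On the assumed inputs it was about 2 to 2.5 points at 12 months and 5 to 7 points at 24 months when only return depended on QOL (β = 0.3), about 4 points at 24 months for slopes -1 and -2 when death did too (both 0.3), and zero when missingness was unrelated to QOL. These figures rest on about a quarter to a third of forms missing among the living and on the assumed slopes and dependence. The registry's actual completion will decide where it falls.

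The consequence is confined to a secondary objective in a descriptive study. It still deserves correction, because QOL is presented as a strength and no comparator is available.

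**What to change.** 1. Keep the while-alive summary and label it as conditional on being alive at each visit.
2. Report change from each patient's own baseline, with the number alive and the number of forms returned beside every estimate.
3. Add a missing-not-at-random sensitivity analysis for forms missing through illness before death. One option is multiple imputation, using earlier follow-up forms as well as baseline, with a downward shift over a stated range such as 5, 10 and 15 points. Given step 6, extend the range until the conclusion changes, since 15 points may be too small at late visits. The alternative is to show trajectories by time to death or dropout. A likelihood-based repeated-measures model alone is not enough, because it also assumes missing at random.
4. State how the recorded reasons decide which forms count as illness-related.
5. Word the QOL imputation as an explicit exception to the general no-imputation rule.

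No new data are needed if the reasons for missing forms are analysed as planned. The cost is a few sentences, modest extra programming and possibly a less favourable QOL result.

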### Data Collection

Patients enter the study by accepting participation and signing the informed consent form. Baseline data is collected upon allocation. Data on how the treatment was performed and its day-of-treatment outcomes are collected on the day of treatment. The patient is then followed for a maximum of 24 months or until study exit (see Figure 1). Guidelines for radioembolization advise that posttreatment assessments should be performed every 3 months [22]. However, the final decisions on treatment and follow-up schedules are determined by the site-specific medical teams.

Baseline assessments included patient demographics, medical history related to the underlying disease and cancer treatment, as well as cancer type and stage for patients with HCC (Table 1). The technical aspects that may determine how radioembolization is performed or impacts procedure-related outcomes were documented at the time of treatment. Time to event end points and safety end points were collected at every follow-up. In addition to demographic and clinical data, patient-reported outcomes are measured using the European Organisation for the Research and Treatment of Cancer (EORTC) quality of life questionnaire C30 (QLQ-C30) [23,24]. The questionnaire was provided before the treatment, shortly after the treatment, and at every follow-up. When this was not feasible on site, patients were approached via letters or phone calls organized by the study center responsible for the patient. For patients with HCC, in addition to the QLQ-C30, the HCC module was provided to assess factors related to chronic liver disease, as well as issues related to the primary tumor and its treatment [25]. The QLQ-C30 and HCC module were made available to each patient in their local language, using questionnaires translated and validated by EORTC [26-28].

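### PFS censoring for withdrawn or lost patients is tied to the last MRI scan, although the registry requires no MRI; if such patients were imaged otherwise, evaluable event-free time is discarded

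*Protocol article*

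**What the plan says.** The Statistical Analysis section gives separate censoring dates for the two survival end points when a patient withdraws consent or is lost. Overall survival is censored when the patient was last seen alive. PFS is censored "at the time of their last magnetic resonance imaging scan from which disease progression could have been determined". No other type of imaging is named there or elsewhere in the article.

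The surrounding text sets these conditions:

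- **Design (Study Design and Objectives):** "CIRT is a prospective, multicenter, single-device, noninterventional study of patients with liver tumors treated with radioembolization in daily routine practice".
- **Follow-up (Data Collection):** a 3-monthly interval is cited as guideline advice, but "the final decisions on treatment and follow-up schedules are determined by the site-specific medical teams".
- **Progression events (Table 1):** the follow-up item is "Date of effectiveness event", with no modality attached.
- **Deaths (Statistical Analysis):** "Patients who die during the course of their follow-up in the registry will be regarded as having disease progression", for both PFS and liver-specific PFS.
- **Loss (Limitations):** loss to follow-up is expected but not quantified: "It will therefore not always be possible for study sites to collect additional follow-up data and the patient will be reported as lost to follow-up".

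The same section also states the intention to analyse whatever data are available, without imputation (quality of life apart).

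**The concern.** The rule sets a different standard of proof for the two kinds of outcome. As far as the text goes, an event needs no MRI: a death counts by itself, and a progression is entered as a date. Event-free time in a withdrawn or lost patient counts only up to an MRI. In a registry that imposes no imaging, such a patient may have had adequate scans of another kind. Applied literally, the rule ignores those scans and moves censoring back to an older MRI, or to the treatment date if there was none.

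At stake are the Kaplan-Meier PFS estimates, a named secondary effectiveness end point, and those for liver-specific PFS if the same rule is carried over. This is not a detail left to a fuller plan. The article states the rule, and an analysis plan that follows it inherits the problem.

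**Working it through.** The article gives no PFS assumption, loss rate or imaging mix, so there is no figure of the plan's own to reproduce. The direction can be derived; the size can only be illustrated.

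**Direction.** The Kaplan-Meier estimate is S(t) = Π(1 − d_j/n_j), with d_j events and n_j patients at risk at event time j. Moving the censoring time of an event-free lost patient earlier changes no d_j and can only lower n_j or leave it alone. Each factor falls or stays equal, and so does S(t) at every t. This requires that the d_j do not depend on modality. If progression seen on other imaging were not accepted either, some d_j would be missed, which pushes S(t) upward, and the net direction is open.

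**Size, closed form.** All inputs are assumptions:

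- true median PFS of 6 months, so λ = ln 2 / 6 = 0.1155 per month;
- constant monthly loss hazard γ;
- a share p of patients with no MRI after treatment, all censored at time 0 if lost (the extreme reading).

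Among patients truly still event-free and under observation at time t, the MRI share (1 − p) stays in the risk set. A patient without MRI stays only if an event will come before loss, which has probability λ/(λ+γ). The apparent hazard is therefore the true hazard multiplied by

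R = 1 / [(1 − p) + pλ/(λ+γ)] = (λ + γ) / (λ + γ(1 − p)),

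and apparent 6-month PFS is 0.5^R. For γ = 0.01 and p = 0.3: R = 0.1255/0.1225 = 1.0245, and 0.5^1.0245 = 49.2%.

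| Monthly loss γ | Loss by 12 months, 1 − e^(−12γ) | R at p = 0.3 | 6-month PFS | R at p = 0.7 | 6-month PFS |
|---|---|---|---|---|---|
| 0.5% | 5.8% | 1.013 | 49.6% | 1.030 | 49.0% |
| 1% | 11.3% | 1.025 | 49.2% | 1.059 | 48.0% |
| 3% | 30.2% | 1.066 | 47.8% | 1.169 | 44.5% |
| 6% | 51.3% | 1.114 | 46.2% | 1.315 | 40.2% |

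The true value is 50% throughout. A simulation with progression detected at 3-monthly scans and a 24-month cap agrees within a point: about 48-49.6% at 0.5-1% monthly loss and 41-48% at 3-6%. The formula ignores the cap, which is why its worst case is slightly lower.

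**Size, second set of assumptions.** A separate simulation used 1047 patients (the enrolled number), exponential PFS, 3-monthly scans, a 24-month cap and 60 replicates per scenario. Loss at 12 months was 10%, 20% or 40%; the share without MRI was 25%, 50% or 75%. It compared median PFS under last-scan-of-any-modality with last-MRI-only censoring:

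- true median 4 months: from 3.96 vs 3.92 (10% loss, 25% without MRI) to 3.8 vs 3.4 (40%, 75%);
- true median 8 months: from 7.9 vs 7.8 (10%, 25%), through 7.8 vs 7.3 (20%, 50%), to 7.5 vs 6.1 (40%, 75%).

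MRI-only censoring gave lower or equal PFS in every replicate, as the algebra requires.

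**The case against.** The strongest reply is that two links in the argument are not in the article. First, it never says that any patient was imaged by something other than MRI. The Data Collection section leaves treatment and follow-up schedules to the sites; it does not describe modalities. Patients may also have had mixed imaging, in which case the last MRI may be only slightly out of date. Second, acceptance of progression from any modality is read from a Table 1 cell that lists when data are collected and does not define progression. Both objections stand, and they make the point conditional. The death rule, however, is explicit and needs no scan.

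A reader might go further and infer that CIRT's PFS is certainly and materially biased downward. The documents do not support this: the loss rate and the share without MRI are unknown, and at 0.5-1% monthly loss the fall at 6 months is only about 0.4 to 2 points. A reader might also infer that the Cox hazard ratios are distorted. That would need imaging modality to vary with the Table 2 covariates, which the article does not show; no hazard ratio has been computed here.

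Finally, the study is descriptive and exploratory, has no comparator, and plans to compare patients lost with those followed. That comparison is useful scrutiny of dropout, but it does not correct a censoring date that ignores usable scans.

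**Conclusion.** The rule is badly fixed as written: it names one modality in a registry that prescribes none, and it can discard evaluable event-free time in patients who withdraw or are lost. If some of those patients were imaged without MRI, and if progression counts whatever the modality, Kaplan-Meier PFS can only fall or stay equal. The size cannot be determined from the article. Under the stated assumptions it runs from under half a percentage point to about 9 points of 6-month PFS (50% to 41%), and from about 0.04 to 1.5 months of median PFS in the second illustration. The upper ends need heavy loss, a large share without MRI, and censoring at time 0 for all of them.

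This should be fixed, but it does not threaten the study. The primary objective describes clinical application and is untouched, as is overall survival.

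**What to change.** In the PFS censoring sentence, replace the reference to an MRI scan with *last imaging assessment of any modality*, and keep the existing condition that progression could have been judged from it. State that the same rule applies to liver-specific PFS, for which the sentence gives no censoring date.

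The text change is one sentence. The cost lies in the data: the rule needs dates of event-free non-MRI scans from the e-CRF. Table 1 does not show that these were captured, and follow-up collection ended in December 2019. Where they were not recorded, report how many withdrawn or lost patients are affected, so that readers can judge the possible effect on PFS.
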